**Fig. 1 Fig1:**
[figure not shown]
The Andromeda Study

Women who agree to participate in Andromeda are asked to fill in a short risk questionnaire (SRQ - Additional file 1) to collect information on general BC risk factors (reproductive and BC family history, previous breast biopsies, basic physical activity level, body mass index and alcohol consumption), immediately at the enrolment desk.

In addition, they are asked to fill in a long risk questionnaire (LRQ - Additional file 2) on diet, physical activity, smoking habits, general state of health and psychological distresses (sections on physical activity and on dietary habits were modified from the EPIC questionnaires [25], the section on psychological distresses was taken from the Brief COPE questionnaire [26]). Women are also invited to undergo anthropometric measurements (height, weight, body composition, and waist circumference) and to provide a blood sample for serum, plasma and buffy-coat storing. Blood specimens are aliquoted, processed and stored at −80 °C. These last procedures can be performed at the time of the examination or at a later date, to be agreed with the woman; fasting is not required.

Mammograms derive either from DM or from DBT (according to the Proteus trial randomization) and are read by two expert radiologists. Breast density is calculated during breast examination, through a specific algorithm [27] and it is classified into categories by means of the Breast Imaging Reporting and Data System (BI-RADS) [28].

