### Statistical power and analysis

All the data collected through the SRQ will be used to obtain the risk estimates based on a risk prediction model that has been developed for the Italian population and validated on an independent cohort of Italian women (Petracci score) [32].

This information, along with the information on breast density, lifestyle related risk, polygenic risk score from miRNAs and SNPs will be modeled in respect of BC risk factors onset.

As they are determined on the same subjects, among women with abnormal mammography, the most efficient estimate of the ratio between relative (positive vs negative) positive predictive values (PPV) ratios, for any couple of the above factors is given by:$$ PPV\; ratios=\frac{cancers\;\left(\kern0em positive to factor1\; but\; not to factor2\right)\kern0.5em \times \kern0.5em non cancers\;\left(\kern0em positive to factor2\; but\; not to factor1\right)}{cancers\;\left(\kern0em positive to factor2\; but\; not to factor1\right)\kern0.5em \times \kern0.5em non cancers\;\left(\kern0em positive to factor1\; but\; not to factor2\right)} $$

Assuming that 40% of 21,000 enrolled women have a dense breast, 20% a certain Petracci score, 50% a lifestyle risk and 20% a given miRNA, that 11‰ of study women carry BC and that the overall PPV of mammography is 20%, some 100–120 discordant cancers and 640–740 discordant women with abnormal mammography but no cancer are expected for the considered couples of factors. Under these assumptions, the study has about 80% power to reject (alpha = 0.05) the null hypothesis that the relative PPV ratio equals 1 if its true value is at least 1.8–2.0, depending on the couple of factors considered.

To calculate the sample size necessary for biomarkers pivotal evaluation (expressed on a continuous scale), minimally acceptable and desirable levels of typical performance measures of interests, such as the true-positive rate (TPR) and the false positive rate (FPR) have been defined. For general population screening, the FPR must be quite low to avoid huge numbers of people undergoing unnecessary costly medical procedures. Thus a maximally acceptable false-positive rate (FPR0) of 4% (the minimally acceptable specificity is therefore 96%) and a minimally acceptable sensitivity of 80% (TPR0) were hypothesized. The null hypothesis to be rejected is the following: H0: TPR0 ≤ 0.80 or FPR0 ≥ 0.04.

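### The single 1.8–2.0 detectable PPV ratio ignores likely overlap between the risk score and the lifestyle criterion, and does not cover that pair if lifestyle is the better predictor

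*Protocol article*

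**What the plan says.** All the relevant power figures are in the protocol article, Statistical power and analysis. The comparison formula is offered for every pair of factors and uses only discordant women, that is, those positive on one factor and negative on the other. The inputs are "Assuming that 40% of 21,000 enrolled women have a dense breast, 20% a certain Petracci score, 50% a lifestyle risk" and "20% a given miRNA", together with the assumption "that 11‰ of study women carry BC" and a mammography PPV of 20%. From these the text states that "some 100–120 discordant cancers and 640–740 discordant women with abnormal mammography but no cancer are expected for the considered couples of factors". It then claims about 80% power at alpha 0.05 "if its true value is at least 1.8–2.0, depending on the couple of factors considered".

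The same section describes where the score comes from: "All the data collected through the SRQ will be used to obtain the risk estimates based on a risk prediction model". Under Enrolment (the text below Fig. 1), the short questionnaire (SRQ) covers reproductive and family history and also "previous breast biopsies, basic physical activity level, body mass index and alcohol consumption". Lifestyle nevertheless appears as a separate criterion with its own 50% prevalence. The article does not say which items define it, and states no assumption about dependence between factors.

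**The concern.** Two features of the power statement look doubtful for the score-versus-lifestyle pair.

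- **Overlap.** If lifestyle items feed the score, women positive on one criterion will tend to be positive on the other. That reduces the number of discordant women, the only ones who inform the estimate. Most affected is the small group positive on the score but not on lifestyle.
- **Direction.** With prevalences of 20% and 50%, the discordant split is lopsided, so power depends strongly on which factor is the better predictor. One range quoted for all pairs hides this.

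Comparing criteria by PPV, alone and in combination, is how the first main aim is to be met. If the design cannot reliably show a two-fold difference for this pair, a non-significant result could be misread as equal predictive value.

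**Working it through.** **Inputs from the protocol.** 21,000 women; 11 per 1,000 with cancer; PPV 20%; prevalences: density 0.40, score 0.20, lifestyle 0.50, miRNA 0.20; alpha 0.05 (sidedness not stated, two-sided used here); power 80%.

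**Input assumed.** The correlation phi between score and lifestyle, both taken as yes/no factors, is not given. I use 0 to 0.3. With these prevalences the maximum is 0.5.

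**Step 1: totals.** Cancers = 21,000 × 0.011 = 231. Abnormal mammograms = 231 / 0.20 = 1,155. Non-cancers = 1,155 − 231 = 924.

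**Step 2: the plan's discordant counts.** Under independence the discordant share is p1(1 − p2) + p2(1 − p1).

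| Pair | Share | Cancers (of 231) | Non-cancers (of 924) |
|---|---|---|---|
| Density with score, or with miRNA | 0.44 | 102 | 407 |
| Lifestyle with any other factor | 0.50 | 116 | 462 |
| Score with miRNA | 0.32 | 74 | 296 |

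The stated 100–120 cancers are therefore reproduced by independence for five of the six pairs. The stated 640–740 non-cancers are not reproduced. They would need 640 / 0.44 = 1,455 to 740 / 0.50 = 1,480 non-cancers, which corresponds to a PPV of 231 / (231 + 1,455) = 13.7% to 231 / (231 + 1,480) = 13.5%.

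**Step 3: power for score versus lifestyle.** P(both positive) = 0.20 × 0.50 + phi × √(0.20 × 0.80 × 0.50 × 0.50) = 0.10 + 0.20 phi. The discordant shares are 0.20 − P (score only) and 0.50 − P (lifestyle only). The non-cancers follow these shares. The discordant cancers are split by the true ratio R (score over lifestyle): odds of score-only = R × (score-only / lifestyle-only among non-cancers). The variance of log R is the sum of the reciprocals of the four cells. Power = Φ(|log R| / SE − 1.96).

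*Score better, phi = 0, R = 2.* Non-cancer cells are 92.4 and 369.6. Cancer odds = 2 × 0.25 = 0.5, so cancer cells are 38.5 and 77.0. SE = √(1/38.5 + 1/77.0 + 1/92.4 + 1/369.6) = 0.229. Power = Φ(0.693 / 0.229 − 1.96) = 86%.

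*Lifestyle better, phi = 0, R = 1/2.* Cancer odds = 0.5 × 0.25 = 0.125, so cancer cells are 12.8 and 102.7. SE = 0.318. Power = Φ(0.693 / 0.318 − 1.96) = 59%.

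| phi | Share of score-positive women who are lifestyle-positive | Discordant cancers / non-cancers | Score better: detectable ratio | Lifestyle better: power at a two-fold ratio |
|---|---|---|---|---|
| 0 | 50% | 116 / 462 | 1.91 | 59% |
| 0.1 | 60% | 106 / 425 | 2.00 | 50% |
| 0.2 | 70% | 97 / 388 | 2.14 | 40% |
| 0.3 | 80% | 88 / 351 | 2.39 | 29% |

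**Step 4: sensitivity.** With about 1,470 non-cancers, the base implied by 640–740, the detectable ratios become 1.85, 1.94, 2.07 and 2.29, and power with lifestyle better becomes 61%, 52%, 41% and 30%. A two-proportion test on 924 non-cancers gives 1.93, 2.03, 2.18 and 2.45. With lifestyle better it gives 62%, 51% and 39% power at phi 0, 0.1 and 0.2. Neither choice changes the picture.

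**The case against.** The strongest reply is that nothing in the article fixes the overlap. The lifestyle criterion is undefined, and the long questionnaire also collects diet, smoking and physical activity, so the criterion may rest largely on items outside the score. The article does not show what weight the score gives to any SRQ item. At phi 0.3, 80% of score-positive women would be lifestyle-positive, which is a lot for a score that also uses reproductive, family and biopsy history. With the score as the better factor and phi up to about 0.1, the detectable ratio is about 2.0, in line with the claim. All of this stands, and it limits the overlap argument to a conditional one. It does not answer the result with lifestyle as the better factor, which needs no correlation.

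Three stronger readings are tempting but not supported:

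- **That overlap alone defeats the power claim.** This would need a correlation that the documents do not give.
- **That the detectable ratio is 2.2–2.9 at phi 0.1–0.3.** A reader gets this by leaving the cancer cells at their null split. A true ratio away from 1 changes that split, and the resulting figures fit neither direction.
- **That shared items are counted twice when the criteria are combined.** The article says the factors will be modelled together and describes no additive scoring; correlated covariates in a joint model are not thereby double-counted.

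**Conclusion.** The point holds in a limited form. The stated cancer counts rest on an independence assumption that the article does not mention and that its description of the score makes doubtful for score versus lifestyle. If the score is the better factor, the claim is met at phi 0, borderline at 0.1, and missed at 0.2 and 0.3 (about 2.1 and 2.4). If lifestyle is the better factor, power at a two-fold ratio is about 59% at best, so 1.8–2.0 is not delivered for this pair whatever the overlap.

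These results assume a two-sided 5% test, 231 cancers, 924 non-cancers, the protocol's prevalences in both groups and the same phi in both. Only the range of phi comes from outside the documents. Separately, and with no assumption about phi beyond the independence that yields the plan's own cancer counts, 640–740 discordant non-cancers contradict the 20% PPV.

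**What to change.** Replace the single range with a table giving discordant cancers, discordant non-cancers and detectable ratio for each pair, in both directions. Show the score–lifestyle pair over a stated range of correlation, and say which questionnaire items form the lifestyle criterion. Include score versus miRNA or state that it is not among the pairs considered, since its 74 discordant cancers fall outside 100–120. In the same correction, either change 640–740 to the counts that follow from a 20% PPV (407–462 under independence for the other five pairs) or correct the PPV assumption.

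Lifestyle need not be redefined to exclude items used in the score. The Background names weight and physical activity among the lifestyle factors of interest, so that would change the exposure being studied.

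The cost is a recalculation and some wording, with no new data. The downside is a less favourable stated detectable ratio for this pair.

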The sample size required with an 80% power (alpha = 5%) and assuming desirable true-positive rate and false-positive rate of TPR1 = 0.90 and FPR1 = 0.05, respectively, was of 179 cases and 537 controls. Sample size computation was based on theory on the Receiver Operating Characteristic (ROC) curve.

Assuming an annual BC detection rate (DR) of 0.006 in the first year and 0.005 in the second year of the study (therefore the biennial DR considered was 0.011) a total of 233 case patients in the first two years of the study are expected to be observed, thus exceeding the 179 required. These estimates are based on DRs observed in the previous years in the same centers considered in this study (Turin, Biella) [4]. Thus, the molecular analyses will be performed on 233 cases and 699 matched controls. For each case, three control subjects will be selected from the cohort of women, on the basis of the following criteria: no history of cancer, similar age at enrolment (within 5 years), similar race, availability of blood sample, similar date of blood draw.

Moreover, circulating miR-18a, miR-181a, and miR-222 levels - derived from the sister study cohort [21] - on plasma collected from all the women enrolled that have at least one first degree relative with BC will be assessed. The estimated number of this subgroup is 1800 women, 40 of which are expected to develop BC within 18 months, and will therefore belong to the case group.

To assess the predictive ability of the considered criteria (i.e., breast density, absolute risk of developing BC and, lifestyles) in identifying groups of women with different risk levels, the positive and negative predictive values and ratios of predictive values (PPV and PPV ratios) will be calculated for each criterion.

The discrimination ability of single biomarkers will be evaluated by means of the ROC curves, whereas to test if biomarker levels are significantly higher or lower in cases and controls, logistic regression models will be used. To evaluate the association between women’s characteristics or tumor features and biomarker level, linear regression models will be adopted.

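### The biomarker power statement is impossible as printed: the alternative FPR1 = 0.05 lies inside the null hypothesis (FPR ≥ 0.04)

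*Protocol article*

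**What the plan says.** All of this is in the Protocol article, Methods/Design, Statistical power and analysis.

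- The false-positive rate has to be low for general-population screening. Its highest acceptable value, FPR0, is 4%, which the text also expresses as a specificity of at least 96%.
- On the other axis, the lowest acceptable sensitivity, TPR0, is 80%.
- The hypothesis is printed as "H0: TPR0 ≤ 0.80 or FPR0 ≥ 0.04".
- With alpha at 5% and power at 80%, the required size is stated this way: "assuming desirable true-positive rate and false-positive rate of TPR1 = 0.90 and FPR1 = 0.05, respectively, was of 179 cases and 537 controls".
- The computation is attributed to ROC theory. The markers are described as continuous. Neither the sidedness of alpha nor an ROC slope is given.
- The expected yield is 233 cases, so the analysis is planned on 233 cases and 699 controls.

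**The concern.** A design alternative should be better than the boundary of the null hypothesis on every axis tested. TPR1 = 0.90 is better than 0.80. FPR1 = 0.05 is worse than 0.04, so the performance called desirable is one that the same section rules out. Power is the probability of rejecting a false null hypothesis, and here the null hypothesis is true at the design point.

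Meeting pre-specified true- and false-positive rates is part of the second main aim (Study aims). As printed, a reader cannot tell whether a marker succeeds by showing an FPR below 4%, by showing adequate sensitivity at an FPR of 4%, or by showing it at 5%. If that is settled after results are known, the success criterion is open to choice.

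**Working it through.** **Inputs, all from Statistical power and analysis.** TPR0 = 0.80, FPR0 = 0.04, TPR1 = 0.90, FPR1 = 0.05, alpha 5%, power 80%; 179 cases and 537 controls required (537 = 3 × 179); 233 and 699 planned (699 = 3 × 233).

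**1. Can 179/537 be reproduced for the printed null hypothesis?** No. Both parts of H0 must be rejected, and the FPR part yields no control number because 0.05 is on the null side of 0.04. One-sample normal formulas for the TPR part, with null and alternative variances, give 83 to 164 cases over a range of alpha and beta splits.

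**2. Rejection probability at the printed alternative.** Any valid 5% test: at most 5%. For a concrete value, assume a fixed positivity threshold and exact one-sided 5% binomial tests.

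- 537 controls: the largest k with P(X ≤ k | 0.04) ≤ 0.05 is 13 (actual size 3.2%). P(X ≤ 13 | 0.05) = 0.2%.
- 699 controls: k = 19 (actual size 4.5%). P(X ≤ 19 | 0.05) = 0.2%.
- The TPR part at 0.90 has 98.0% power with 179 cases and 99.7% with 233, so the failure comes wholly from FPR1.

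**3. Same joint test with an FPR1 that lies outside H0.** The documents give no such value, so these are assumptions. TPR1 = 0.90; joint power is the product of the two parts.

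| Assumed FPR1 | 179/537 | 233/699 |
|---|---|---|
| 0.03 | 0.980 × 0.262 = 26% | 0.997 × 0.384 = 38% |
| 0.025 | 52% | 70% |
| 0.02 | 0.980 × 0.807 = 79% | 0.997 × 0.926 = 92% |

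**4. Test of sensitivity at a fixed FPR = f, H0: ROC(f) ≤ 0.80 against 0.90.** The variance per case, with three controls per case, is V = TPR(1 − TPR) + r² f(1 − f)/3, where r is the ROC slope at f. The slope is not in the documents; I assume an equal-variance binormal curve, so r = φ(Φ⁻¹(TPR))/φ(Φ⁻¹(f)).

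- f = 0.04, one-sided, null variance only: r = 3.249 and V₀ = 0.16 + 3.249² × 0.0384/3 = 0.295. n = (1.645 + 0.842)² × 0.295/0.1² ≈ 182 cases.
- f = 0.05, two-sided, null and alternative variances: V₀ = 0.277 (r = 2.715) and V₁ = 0.09 + 1.702² × 0.0475/3 = 0.136. n = (1.960√0.277 + 0.842√0.136)²/0.1² ≈ 180 cases.
- f = 0.04, other choices: 147 (one-sided, both variances), 192 (two-sided, both variances), 232 (two-sided, null variance only). The alternative variance alone gives 89 (one-sided) and 113 (two-sided).

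So 179 is close to two different calculations, one at f = 0.04 and one at f = 0.05. The documents do not say which, if either, was used.

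**5. Could FPR0 and FPR1 simply have been exchanged?** Testing FPR ≥ 0.05 against 0.04 needs (1.645√(0.05 × 0.95) + 0.842√(0.04 × 0.96))²/0.01² ≈ 2,740 controls (one-sided, 80% power). An exchange does not recover 537 under the joint test.

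**The case against.** The strongest reply is that the markers are continuous and the size rests on ROC theory, so a fixed-threshold binomial test is not what the protocol describes. For a continuous marker, asking whether some threshold gives TPR above 0.80 with FPR below 0.04 amounts to asking whether ROC(0.04) exceeds 0.80. A joint null and an ROC calculation are therefore compatible. This stands, and the 0.2% must be read only as the literal fixed-threshold case.

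It also removes a conclusion that a reader might draw: that a marker performing at the desirable level would be declared unacceptable. The threshold can move. On an equal-variance binormal curve through (0.05, 0.90), a = 1.282 + 1.645 = 2.926, so ROC(0.04) = Φ(2.926 − 1.751) = 0.88, and a TPR of 0.80 is reached at an FPR of about 0.019. Such a marker has operating points outside H0. Its power against ROC(0.04) ≤ 0.80 with 179/537 is 51% to 82%, depending on sidedness and variance form.

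The reply does not rescue the text. A fixed-FPR test has no separate FPR1, and if f was 0.05, the marker is judged at a rate that the section calls unacceptable. Nor is this an omission that a condensed article may leave to a fuller protocol: null, alternative, power and size are all printed, and they cannot all be true.

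**Conclusion.** The contradiction is certain and needs no assumption: FPR1 = 0.05 satisfies FPR ≥ 0.04, so 80% power at the printed alternative is impossible at any sample size. The bound is 5%. The sharper figure of 0.2% assumes a fixed threshold and a one-sided exact test.

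A reader might go on to infer that 179/537, or the planned 233/699, is too small. The documents do not support that. Fixed-FPR ROC calculations land near 179 under some unstated but ordinary assumptions, and the planned sample is larger. Nor do the documents show which of the printed figures is the wrong one. The defect is in the statement of hypothesis and power, for part of a main aim. It must be corrected before the result is tested.

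**What to change.** Before the assays are unblinded, reconcile FPR0, FPR1 and H0 according to the calculation actually made.

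- If it was a fixed-FPR ROC test, restate it as H0: ROC(f) ≤ 0.80 against ROC(f) = 0.90, with a single f consistent with the stated 4% maximum, and remove the separate FPR1.
- If the joint null is kept, state an FPR1 below 0.04, chosen on its merits and not fitted to the number of controls.

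In either case state the sidedness of alpha and the assumed ROC slope, and restate power for 179/537 and for 233/699.

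The cost is wording and one recalculation; the remedy is to restate the figures, not to enrol more women. It may still have a consequence: under the joint null with a fixed threshold, the target that 233/699 can support with at least 80% power is nearer FPR1 = 0.02 than 0.03, which is materially stricter than the printed 0.05, and the report should say so.

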**Methods:**

About 21,000 women aged 46–67 years compliant to screening mammography are expected to be enrolled. At enrolment, information on well-known breast cancer risk factors and life-styles habits are collected through self-admistered questionnaires. Information on breast density and anthropometric measurements (height, weight, body composition, and waist circumference) are recorded. In addition, women are requested to provide a blood sample for serum, plasma and buffy-coat storing for subsequent molecular analyses within the nested case-control study. This investigation will be performed on approximately 233 cases (screen-detected) and 699 matched controls to evaluate SNPs and circulating microRNAs. The whole study will last three years and the cohort will be followed up for ten years to observe the onset of new breast cancer cases.

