## Background

Breast cancer (BC) represents the most frequent neoplasm in women worldwide, with nearly 1.7 million new cases diagnosed in 2012 [1]*.* In Italy about 1 out of 3 malignant cancers in women (30%) is a BC (with the exception of cutaneous tumors) as reported by Italian cancer registries between 2008 and 2012. They also estimated that in 2016 about 50,000 women would have been diagnosed with BC [2]*.* Mammography is the preferred screening test for early detection of breast cancer and has been studied in more than 600,000 women in 10 randomized trials over the past 50 years [3].

In Italy, mammography screening for early diagnosis has been implemented on a regional basis in several Italian areas. In compliance to national and international screening guidelines, most programs invite women aged 50–69 years to undergo a mammography, every two years [4].

Although mammography has become a standard of detection in BC screening, its limitations are well recognized. In the last decade, mammography BC screening has been the subject of controversy, with several researchers questioning whether the benefit in terms of mortality reduction is large enough to justify the recognized harms of screening, in particular over-diagnosis [5, 6]. Other researchers have provided overviews of the accumulated evidence and concluded that the pros outweigh the cons [7]. The ongoing discussion has led to a lack of clear guidance to both women and their physicians as to whether women should attend mammography screening.

In virtually all population-based BC screening programs, the only risk factor – even though the strongest – used to define the target population is age. This ‘one-size-fits-all’ screening approach has been criticized, as information are gradually becoming available on the advantages of personalized screening, based on appropriate risk stratification [8–14].

A tailored approach can make screening for BC more effective and efficient by targeting women at higher risk, who are most likely to benefit, and reducing exposure to screening in those women at lower risk, who are more likely to experience the harms.

The development of a comprehensive risk prediction model with improved discriminatory power over current models to classify the population into meaningful risk groups will enable the screening strategies to target those at high-risk while reducing interventions in those at low-risk.

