### Study setting

The eligible population of the study consists of 46–67-year-old women invited to breast screening in the cities of Turin and Biella (two Northern Italian cities in Piedmont), where BC screening is a long-standing practice well known by the people living in the area [4]. For organizational reasons the Andromeda study is conducted simultaneously with another investigation, the Proteus study (NCT02590315), a randomized controlled trial aimed at comparing the performance of digital breast tomosynthesis (DBT) with those of standard digital mammography (DM). The study duration is planned for three years. Enrolment started in July 2015 and by the end of the recruitment phase (December 2017) about 21,000 women are expected to be included in the study. The women cohort will be followed up for additional ten years after the study ending through the screening archives to observe the onset of new BC cases.

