### Biomarkers analysis

The Andromeda study includes molecular analyses to evaluate circulating miRNAs and SNPs that will be performed blindly on an appropriate case-control sample extracted from the cohort of enrolled women, as soon as a minimum number of BC cases will be reached. Blinding allows avoiding that knowledge of subject’s outcome status affect the interpretation of an assay result or the care with which the specimen is handled. The prospective specimen collection plus retrospective blinded-evaluation (PRoBE) design assumed here has been proposed by Pepe et al. [29] as a good practice to follow for the pivotal evaluation of biomarker accuracy.

The selected miRNAs come from two consolidated studies [20, 21], and are suited to the screening nature of the Andromeda study.

In more detail the biomarkers to be analyzed are the following:Circulating total RNA extraction from plasma samples will be carried out with miRNeasy serum/plasma minikit (Qiagen) with minor modifications of the Exiqon protocol, implying use of a RNA carrier (batteriofage MS2 RNA, Roche Diagnostics®) to promote RNA precipitation. Cel-miR-139 will be used as spike-in control to check extraction yield and to normalize data. RNA samples will be purified on membranes and eluted with nuclease free water and stored at −80 °C. We will carefully evaluate the presence of haemolysis in our analysis and exploit our huge sample cohort to validate previous results on an independent dataset.RT-qPCR analysis of selected markers (genes, microRNAs, lncRNAs)Total RNA samples will be reverse-transcribed and amplified with specific assays for cel-miR-39, hsa-miR-1228, hsa-miR-145, hsa-miR-451, hsa-miR-222, hsa-miR-18a, hsa-miR-181a and analyzed on a qPCR apparatus with specific dedicated software. Every RNA samples will be analyzed in triplicate. Normalization of expression data will be carried out using hsa-miR-1228 [30] and cel-miR-39 as normalizers. As for SNPs also for miRNAs research findings are continuously updated, so they will be selected considering the most recent findings at the time of their extraction [31].SNP genotypingGenomic DNA will be extracted from buffy coat with High Pure PCR Template preparation kit (Roche Diagnostics®). 77 SNPs described in Mavaddat et al. [18] will be evaluated using the Personal Genome Machine (Ion Torrent) NGS apparatus.

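### The projection of 233 cases in two years adds two annual detection rates and applies the sum to all 21,000 women, which the enrolment calendar does not allow; the claim to exceed the required 179 within that time is unsupported

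*Protocol article*

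**What the plan says.** All places are in the protocol article.

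- **Statistical power and analysis** requires 179 cases and 537 controls for 80% power in the biomarker evaluation. The case projection starts from "Assuming an annual BC detection rate (DR) of 0.006 in the first year and 0.005 in the second year of the study", adds the two rates, and concludes: "therefore the biennial DR considered was 0.011) a total of 233 case patients in the first two years of the study are expected". It then says that this exceeds the 179 required, and sets the molecular analysis at 233 cases and 699 controls.
- **Abstract, Methods** repeats the set as "approximately 233 cases (screen-detected) and 699 matched controls".
- **Study setting** gives the calendar. For the close of recruitment it says: "by the end of the recruitment phase (December 2017) about 21,000 women are expected to be included in the study". The opening is given in the same place: "Enrolment started in July 2015".
- **Background** gives the only screening interval in the article: "most programs invite women aged 50–69 years to undergo a mammography, every two years". This describes Italian programmes in general.
- **Study aims** lists the detection rate among the screening indicators, next to recall rate and biopsy ratio.
- **Biomarkers analysis** starts the molecular work "as soon as a minimum number of BC cases will be reached", without giving the number.

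**The concern.** A screen-detected case can arise only when a woman is screened. If women attend about once in two years, those screened in study year 1 and those screened in year 2 are different women. The two rates then average to about 0.0055 over the women; they do not add to 0.011 for each woman. Adding them is correct only if the same women are screened in both years, and the full cohort does not exist until about month 30.

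The comparison of 233 with 179 is the article's only assurance that the second main aim will have enough cases for its stated power. If the projection is too high, the molecular analysis either runs on fewer cases than required or starts later than the text implies.

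**Working it through.** **Inputs.** 21,000 women, enrolled July 2015 to December 2017, about 30 months (Study setting). Rates 0.006 and 0.005; 179 cases required (Statistical power and analysis). Two-year interval (Background, general statement). Even accrual is my assumption: 21,000 / 30 = 700 women a month, so 8,400 by month 12 and 16,800 by month 24.

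**1. The plan's figure.** 21,000 x (0.006 + 0.005) = 231, printed as 233 (an exact 233 needs 233 / 0.011 = about 21,180 women). Three controls per case: 3 x 233 = 699. The sum was therefore applied to the whole cohort.

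**2. Expected cases by month 24.**

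| Reading | Arithmetic | Cases |
|---|---|---|
| One screen each, rates by study year | 8,400 x 0.006 + 8,400 x 0.005 | 92 |
| One screen each, higher rate throughout | 16,800 x 0.006 | 101 |
| Yearly screening of everyone | 16,800 x 0.006 + 8,400 x 0.005 | 143 |
| 11 per 1,000 at a single screen | 16,800 x 0.011 | 185 |

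If timing is ignored and all 21,000 enrolment screens are counted, the result is 21,000 x 0.0055 = 116 to 21,000 x 0.006 = 126. To reach 179 from one screen per woman, the rate per screen would have to be 179 / 21,000 = 0.0085, or 179 / 16,800 = 0.0107 by month 24.

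**3. Expected cases by month 36.**

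- Two-yearly screening, with second screens of the 8,400 first-year enrolees at 0.005: 115.5 + 42 = 158 to 126 + 42 = 168. With 0.006 at the second screen as well, 126 + 50.4 = 176.
- Yearly screening: 21,000 x 0.006 + 16,800 x 0.005 = 210.

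**4. When 179 is reached under two-yearly screening with full re-attendance.** Second screens start at month 24 at 700 a month.

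- From 126: (179 - 126) / 0.005 = 10,600 screens; 10,600 / 700 = 15.1 months; month 39.
- From 115.5: (179 - 115.5) / 0.005 = 12,700 screens; 12,700 / 700 = 18.1 months; just past month 42.

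This gives about month 39 to 43.

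**5. Power at the smaller number.** The article does not print its formula. A test of the ROC curve at a false-positive rate of 0.05, equal-variance binormal, 1:3, two-sided 5%, true-positive rate 0.80 against 0.90, has variance per case 0.2767 under the null and 0.1359 under the alternative. The required number is (1.96 x 0.526 + 0.842 x 0.369)² / 0.10² = 179.9, which matches 179. Under that inferred formula, power is about 0.55 at 116 cases and 0.60 at 126.

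**The case against.** **The rate may not be per screen.** The article calls the rates annual, does not define the denominator, and elsewhere assumes that 11 per 1,000 study women carry breast cancer. The two-year interval is stated for most Italian programmes at ages 50–69, while the cohort is aged 46–67. This stands as a limit on the exact figures. It does not rescue the projection. Yearly screening of everyone still gives only 143 by month 24. Only 11 per 1,000 at a single screen passes 179 (185), and even that misses 233. It also conflicts with the article's own derivation of 0.011 as the sum of two annual rates.

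**Even accrual is assumed.** True; no accrual curve is given. But 116 to 126, from all enrolment screens, does not use it, and is also below 179.

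**The analysis can wait.** It starts when a minimum number of cases is reached, follow-up runs ten further years, and the three-year results are called preliminary. This stands. A reader might infer that the second aim will be underpowered, or that 179 cannot be reached within the three-year study. The documents do not support either. Yearly screening would give 210 by month 36, and under two-yearly screening a slow yield delays the analysis; it lowers power only if the analysis is run early.

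**The power figures are not the plan's own.** Also true. They rest on a two-sided formula that was inferred because it reproduces 179. The null hypothesis is worded in one direction, and with a one-sided 5% test the same formula needs about 138 cases.

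**Conclusion.** The projection is wrong as written. No reading of the plan's own rates, combined with its 30-month enrolment (taken as even), gives 233 cases within two years. The credible readings give about 92 to 101 (one screen each) or 143 (yearly screening) by month 24, and 116 to 126 from all enrolment screens. The statement that the required 179 is exceeded in that time is therefore unsupported.

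The finding concerns the two-year projection. Whether 179 is reached by month 36 depends on a screening interval that the article does not state for its own cohort: about 158 to 168 if two-yearly, 210 if yearly. Under two-yearly screening with full re-attendance, about month 39 to 43 is realistic.

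All these counts suppose that every case gave blood. The Discussion calls acceptance of the blood test a critical aspect, so usable cases can only be fewer.

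**What to change.** 1. In Statistical power and analysis, replace the summed rate with rate per screen times women screened by each date. Define the denominator of the detection rate, and state the screening interval that applies to this cohort, including women under 50.
2. Remove the claim that the expected number exceeds 179.
3. Then do one of two things. Either restate power for the attainable number, using the formula that actually produced 179 and printing it (about 0.55 to 0.60 at 116 to 126 cases if it was the two-sided formula above). Or set the trigger in Biomarkers analysis at the required number of cases with plasma, and give a realistic date that uses the follow-up already planned.
4. Correct 233 and 699 to match in Statistical power and analysis and in the Abstract.
5. Check the 11 per 1,000 in the predictive-value power calculation. It equals the same sum, and 231 x 0.44 to 231 x 0.50 = 102 to 116 is consistent with the 100 to 120 discordant cancers stated there. (For two independent factors, 40% and 20% prevalence give 0.4 x 0.8 + 0.6 x 0.2 = 0.44 discordant; 50% with any other gives 0.50.)

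The cost is rewording, together with a less favourable case count, power or analysis date. No extra women or procedures are needed.
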